### Ethics approval

This study is approved by the Institutional Review Board (IRB) of the University of California, Los Angeles (UCLA IRB #24–0663), and is registered at the U.S. National Institutes of Health (clinicaltrials.gov) # NCT06572423. The current protocol is version 1.6. This manuscript adheres to the guidelines and methodology outlined in the SPIRIT checklist.

### Aims

#### Primary aim

To evaluate the 1-year local tumor control of PULSAR for patients with de novo or recurrent, localized or metastatic head and neck cancer who are ineligible for or decline standard of care treatment(s), including standard of care SBRT.

#### Secondary aims

##### Secondary Aim 1

To evaluate the safety and toxicity of PULSAR as local treatment for patients with de novo or recurrent, localized or metastatic head and neck cancer who are ineligible for or decline standard of care definitive treatment(s).

##### Secondary aim 2

To evaluate the 1-year disease progression-free (PFS) and overall survival (OS) of patients with de novo or recurrent, localized or metastatic head and neck cancer who are ineligible for or decline standard of care treatment(s) who receive PULSAR.

##### Secondary aim 3

To evaluate the symptomatic impact of PULSAR as local treatment for patients with de novo or recurrent, localized or metastatic head and neck cancer who are ineligible for or decline standard of care definitive treatment(s).

##### Secondary aim 4

To determine the frequency of re-simulation and/or adaptive planning required with PULSAR.

##### Secondary aim 5

To evaluate standard of care tumor and organs-at-risk (OARs) dosimetry with PULSAR.

##### Secondary aim 6

To evaluate the safety and efficacy of combination PULSAR and cancer-directed systemic therapy in enrolled patients receiving cancer-directed systemic therapy.

### Patient selection

#### Study population

Patients with a diagnosis of primary or recurrent head and neck cancer who are ineligible for or decline standard of care definitive (i.e., curative) treatment(s), including standard of care stereotactic body radiation therapy (SBRT). Reasons for ineligibility for standard of care definitive treatments include locally advanced disease not amenable to standard definitive treatment(s) (e.g., due to the anticipated morbidity associated with definitive treatment), presence of metastatic disease, and medical comorbidities and/or poor performance status that preclude definitive treatment. Additionally, patients with primary or recurrent localized head and neck cancer who are candidates for but decline standard of care definitive treatment(s) will be eligible for enrollment.

#### Inclusion criteria

 ≥ 18 years old.Diagnosis of primary or recurrent, localized or metastatic (AJCC 8th Edition stages I-IV) head and neck cancer. In primary diagnosis cases, pathologic confirmation is required. In recurrent and/or metastatic diagnosis cases, pathologic confirmation is not required if not beneficial to the patient as standard of care, and diagnosis can be assumed based on clinical and/or radiographic evidence.Ineligible for or declines standard of care definitive treatment(s), which will be documented in the patient’s trial screening progress note in their electronic medical record by the treating physician.Measurable disease within the head and/or neck clinically and/or on imaging studies (CT, PET, MRI) within 30 days from date of enrollment.Patient maximum tumor(s) or tumor bed in postoperative patients, diameter must be less than 10 cm.In a woman of childbearing potential, a negative serum or urine pregnancy test within 1 week of treatment start must be documented. Women of childbearing potential must agree to use adequate contraception (hormonal or barrier method of birth control; or abstinence) for duration of study participation and for up to 4 weeks following the study treatment.Patients with a tracheostomy and/or a percutaneous endoscopic gastrostomy tube are eligible for inclusion.

#### Exclusion criteria

Pregnant or breast-feeding.More than 1 prior radiation treatment course directed to the treatment area over the patient’s lifetime. In patients who have received 1 prior radiation treatment course directed to the treatment area, that prior radiation treatment course must have concluded at least 6 months prior to trial enrollment.Any comorbidity or condition which would limit full compliance with the protocol.

### Registration and enrollment process

#### General guidelines

Patients with primary or de novo, localized or metastatic, HNC who are not eligible for or decline standard of care definitive treatment(s) will be informed of this clinical trial if eligible. The decision to participate will be voluntary. Eligible patients who decide not to participate will be offered alternative palliative radiation therapy regimens, systemic therapy (per their medical oncologist), alternative clinical trials, or palliative/hospice care. Information regarding this research study will be included on the UCLA Health Clinical Trials webpage and Clinicaltrials.gov.

#### Registration process

When feasible, an informed consent form in the patient’s preferred language will be given to the patient, or surrogate or legal-authorized representative when applicable, for review. Consent will be obtained after a clear and thorough discussion between the patient, or surrogate or legal-authorized representative when applicable, and the study investigator in clinic in the patient’s preferred language, utilizing a certified interpreter when necessary. To register a patient, the research coordinator will obtain or collect: (1) confirmation of diagnosis of HNC per inclusion criteria above; (2) signed informed consent form; (3) signed HIPAA authorization form. The informed consent form is provided in the Supplemental Material.

#### Pretreatment evaluations

Upon confirmation of eligibility and enrollment in the study, the following will be obtained prior to treatment (if not already performed):

Medical history and clinical examination including weight and ECOG Performance StatusSerum creatinine/estimated GFR within 60 days of CT simulationUniversity of Washington Quality of Life (UW-QoL) and Functional Assessment of Cancer Therapy Head and Neck (FACT-H&N) validated questionnaireFor patients who have received and/or are currently receiving cancer-directed treatment(s), evaluation for existing treatment-related toxicities as measured by the National Cancer Institute Common Terminology Criteria for Adverse Events Version 5.0 (CTCAE v5.0), as this version is currently implemented in our institution’s electronic medical record system which allows for easier and more consistent data documentation and recording.

Additional pretreatment studies including blood tests, imaging, and pathologic evaluation of tumor tissue for Human Papillomavirus and/or p16 positivity may be obtained per standard of care guidelines and/or the patient’s treatment team’s discretion.

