## Background

A significant proportion of patients with de novo or recurrent head and neck cancer (HNC) will not be candidates for standard of care definitive treatment(s) [1–3], which includes a combination of surgery, radiation therapy, and/or systemic therapy, and in some cases, standard of care stereotactic body radiotherapy (SBRT). Common contraindications for standard definitive treatment for HNC include locally advanced disease not amenable to definitive treatment because of the anticipated morbidity with primary or salvage treatment, poor performance status, presence of metastatic disease, or patient treatment preferences [4, 5]. In such cases, locoregional palliative radiation therapy is often utilized given the frequent accompanying symptoms of HNC such as pain or difficulty breathing or eating [6], with the most common HNC palliative radiation therapy regimens being the RTOG-8502 regimen (“quad-shot”) [7–9] and SBRT [10]. While these current palliative radiation therapy options can provide adequate symptom improvement, there are some limitations with these regimens as well.

With quad-shot, there are logistic challenges for both providers and patients given the twice-daily treatments, albeit for just two days total. Moreover, typically multiple cycles are needed to achieve maximal symptomatic benefit, although only about 50% of patients will be able to complete three or more cycles at which point the palliative response rate of this regimen is significantly increased [8, 11–13]. Additionally, while newer radiation therapy techniques such as intensity modulated radiation therapy (IMRT) have been employed to enhance the quad-shot regimen, it represents an older radiation therapy practice which may not fully leverage more recent advances in radiation therapy technology. Regarding SBRT, there is the possibility for severe toxicity, minimization of which is important in the palliative setting, as well as efficacy concerns, particularly for larger tumors or in the re-irradiation setting [6, 14–16]. However, a main limitation across all palliative radiation therapy regimens is suboptimal local control. Local tumor progression negatively impacts symptoms and possibly overall survival given the frequency at which locoregional tumor progression causes death in patients with HNC [17–19].

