## Methods/design

### Study design

This is a single-center (UCLA), single-arm, prospective phase II study with a safety lead-in. 43 subjects are planned. Each subject will receive the same PULSAR radiation therapy course as described below. The first 15 enrolled patients will be evaluated in the safety lead-in portion. If 5 or more of these 15 patients experience CTCAE v5.0 grade 3 or 4 or any patient experiences a grade 5 toxicity probably attributable to PULSAR during or within three months after completion of PULSAR, the study will be stopped for safety concerns; otherwise, the study will proceed, and those initial 15 patients will be included in the 43 subject sample. The trial schema is shown in Fig. 1.

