#### Safety lead-in/interim analysis

The study includes a safety lead-in portion, with formal evaluation on enrollment of the 15^th^ subject. The trial will be stopped if 5 or more patients in the safety lead-in portion experience a serious adverse event, defined as a CTCAE v5.0 grade 3 or 4 toxicity, or if any patient experiences a grade 5 toxicity probably attributable to the intervention during or within three months after completion of PULSAR.

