#### Safety analyses

Safety analyses will be performed for patients included in analysis set SAS. Percentage of patients with acute or chronic grade 3 or higher treatment-related toxicity, incidence of AEs, clinical laboratory information, vital signs, ECOG performance status, and weight, will be tabulated and summarized. Incidence of AEs will be summarized overall and with separate summaries for SAEs, AEs leading to discontinuation, AEs leading to death, etc. The overall safety and tolerability will be assessed throughout the study period. All AE data will be listed individually by patient identifier.

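### Pretreatment CTCAE grading covers only treatment-related toxicity in already treated patients, so tumour symptoms have no standard baseline grade against which to judge grade 3 events on study

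*Protocol article*

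**What the plan says.** Under Pretreatment evaluations, every patient has a history, examination, weight, ECOG status, UW-QoL and FACT-H&N. CTCAE v5.0 grading is narrower. It applies to "patients who have received and/or are currently receiving cancer-directed treatment(s), evaluation for existing treatment-related toxicities", so it is limited both by who is graded (patients with past or current cancer treatment) and by what is graded (effects of that treatment).

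The Background describes the population by its symptoms: "locoregional palliative radiation therapy is often utilized given the frequent accompanying symptoms of HNC such as pain or difficulty breathing or eating". The Inclusion criteria add that "Patients with a tracheostomy and/or a percutaneous endoscopic gastrostomy tube are eligible for inclusion".

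On-study CTCAE grades are then used in three places:
- The lead-in rule in Study design: "If 5 or more of these 15 patients experience CTCAE v5.0 grade 3 or 4 or any patient experiences a grade 5 toxicity". The Safety lead-in/interim analysis section words it as patients who "experience a serious adverse event, defined as a CTCAE v5.0 grade 3 or 4 toxicity, or if any patient experiences a grade 5 toxicity".
- The secondary endpoint of grade 3 or higher treatment-related toxicity, up to 24 months after PULSAR.
- The Safety analyses, which tabulate "Percentage of patients with acute or chronic grade 3 or higher treatment-related toxicity".

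None of these refers to the patient's grade before treatment.

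**The concern.** In head and neck cancer, pain, swallowing difficulty and airway narrowing can come from the tumour or from radiation, and the same CTCAE terms describe both. A grade 3 entry during PULSAR could be a tumour symptom that was already grade 3, a grade 2 symptom that worsened, or a new radiation effect. A starting grade on the same scale is the usual way to tell these apart, and the protocol asks for one only for a different class of finding in a subset of patients.

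Two safety outputs depend on the distinction: the decision to stop or continue after 15 patients, and the grade 3 or higher endpoint. Errors can go either way. An old tumour symptom may be counted as PULSAR toxicity, or a real worsening may be put down to the tumour. The article itself says that safety and feasibility must be validated before larger efficacy studies in this disease.

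**Working it through.** **Step 1. What is graded before treatment, as written**

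| Patient | Effect of earlier treatment | Tumour symptom |
|---|---|---|
| Prior or current cancer treatment | CTCAE grade required | not required |
| Untreated | not applicable | not required |

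**Step 2. What else could serve as a reference**

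- *Adverse events* and *AE evaluation* ask for start and stop dates and for changes in severity at each visit, so a symptom that began before enrollment can often be recognised.
- Table 2 accepts an event as probably related only if its timing fits and the patient's clinical state is an unlikely explanation.
- History, examination, UW-QoL and FACT-H&N are collected from everyone. A tracheostomy or feeding tube would be evident from the first two.

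These allow many events to be classed. None yields a CTCAE grade, so any baseline grade has to be reconstructed afterwards, without a common standard.

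**Step 3. Sensitivity of the 5-of-15 rule**

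The document gives no operating characteristics for the rule, so there is no stated figure to reproduce. Inputs: n = 15 and threshold 5, from Study design. The grade 5 trigger is left out. With p the rate at which patients are counted as having a grade 3 or 4 event:

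P(stop) = sum over k = 5 to 15 of C(15,k) p^k (1−p)^(15−k)

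| p | 10% | 15% | 19% | 20% | 30% | 40% |
|---|---|---|---|---|---|---|
| P(stop) | 1.3% | 6.2% | 13.9% | 16.4% | 48.5% | 78.3% |

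**Step 4. Illustration of misclassification**

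The document does not say how many patients enter with a grade 3 tumour symptom, or how many of these would be misjudged. Let t be the true PULSAR rate and a the assumed share of all patients affected, independent of t.

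*Wrongly counted:* p = 1 − (1−t)(1−a). For t = 10% and a = 10%, p = 1 − 0.90 × 0.90 = 19%.

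| a | 0 | 2.5% | 5% | 10% | 20% |
|---|---|---|---|---|---|
| P(stop), t = 10% | 1.3% | 2.9% | 5.5% | 13.9% | 41.5% |
| P(stop), t = 20% | 16.4% | 21.9% | 28.1% | 41.5% | 67.8% |

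*Masked:* p = t(1−a). For t = 40% and a = 20%, p = 0.40 × 0.80 = 32%.

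| a | 0 | 10% | 20% |
|---|---|---|---|
| P(stop), t = 30% | 48.5% | 38.1% | 28.1% |
| P(stop), t = 40% | 78.3% | 67.8% | 55.2% |

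In patients, moving from 10% to 19% means 15 × 0.09 = 1.35 more counted events on average.

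**Step 5. How often one event decides**

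A single misclassified patient can change the decision when the correct count is 4 (one added) or 5 (one lost).

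- p = 10%: C(15,4) × 0.1^4 × 0.9^11 + C(15,5) × 0.1^5 × 0.9^10 = 0.043 + 0.010 = 5.3%.
- p = 20%: C(15,4) × 0.2^4 × 0.8^11 + C(15,5) × 0.2^5 × 0.8^10 = 0.188 + 0.103 = 29.1%.

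These figures show how sensitive the rule is. They do not show how often misclassification would occur.

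**The case against.** The strongest reply is that the protocol already separates tumour from treatment. The secondary endpoint and the Safety analyses count treatment-related toxicity, not every grade 3 finding. An unchanged symptom present before fraction 1 should fail the timing test in Table 2, and onset dates would expose it. Every patient has a documented pretreatment history and examination and two symptom questionnaires, and the questionnaires are repeated at follow-up. Treatment-emergent definitions and shift tables are commonly left to an analysis plan. The trial calendar (Fig. 2) could not be seen and might list a baseline toxicity assessment.

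Much of this stands. A reader might infer that grade 3 findings on study cannot be classified at all, or that the lead-in rule works on raw grades with no safeguard. The document does not support either reading. Nor does it support any particular rate of misattribution, or a demonstrated difference in bias between untreated and previously treated patients.

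Three things remain. The limit on baseline grading is stated in the text, so it is not a detail left to another document. If Fig. 2 does list a wider assessment, the two places need to be reconciled. The attribution judgement is itself easier to make and to audit with a starting grade. It is also not beyond doubt that the attribution filter covers grades 3 and 4 in the lead-in rule, because the attribution phrase there can be read as attached to grade 5 only. That wording is a separate matter, and this point does not depend on it.

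**Conclusion.** The point holds as a gap in baseline data collection. Followed as written, the protocol leaves tumour-caused symptoms without a standard starting grade in every patient, and leaves untreated patients with no baseline CTCAE grade, in a population expected to be symptomatic. Existing safeguards reduce the consequence without removing it.

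The size of the consequence is unknown. The stopping probabilities are exact for a given counted rate, but the misclassified shares are assumptions, as is their independence of true toxicity. Simply adding 10 points to a true 10% rate would give 16.4%; allowing for patients who have both gives 13.9%. Neither is a forecast.

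A reader might also conclude that events should count only when they exceed the patient's own baseline grade. That does not follow. A patient who enters at grade 3 for a term could then count only at grade 4 or 5 for it, which could weaken the lead-in rule. The one-year local control endpoint and the sample size are not affected.

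**What to change.** - **Pretreatment evaluations:** require CTCAE v5.0 grading of all existing signs and symptoms in every patient before fraction 1, whatever their cause and whatever the prior treatment. Bring the trial calendar into line if it differs.
- **Safety analyses:** report shift from baseline grade beside worst grade and attribution.
- **Lead-in rule:** leave the event definition unchanged, but give the baseline grade to those who assess attribution.

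The cost is one CRF page and a few minutes of grading at an examination every patient already has, plus a sentence or two of protocol text. It should be in place before further patients start treatment, because a baseline grade recorded at the time cannot be recovered once fraction 1 has been given.

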### Intervention

#### Radiation simulation

After confirmation of eligibility, enrolled patients will undergo radiation CT simulation and planning per standard of care. IV contrast will be administered with CT simulation at the treating physician’s discretion though is not required. A thermoplastic face mask will be used for immobilization. HyperArc© technology will be used for treatment planning given prior internal validation of its superiority as above.

#### Radiation planning

For unresectable patients, the treating physician will delineate the gross tumor volume (GTV). For resected patients, a clinical target volume (CTV) will be delineated. The target will include the preoperative tumor volume with up to 5mm expansion for microscopic disease, with considerations for postoperative anatomical changes. Relevant previously obtained imaging studies may be fused to the CT simulation images as deemed necessary by the treating physician to further delineate the GTV or CTV. The GTV or CTV will be expanded by 3–5 mm for treatment setup error. This expansion will comprise the planning target volume (PTV). The dose will be prescribed to cover at least 95% of the PTV unless under-dosing of the PTV is required to meet constraints to OARs. Delineation of normal structures will be performed, including but not limited to: larynx, spinal cord, mandible, brainstem, skin, oral cavity, and parotid gland.

#### OAR dose constraints

No Prior Radiation Therapy to Tumor/Tumor Bed Site: will use max dose point constraints (defined as dose to 0.035 cm^3^) from the AAPM Task Group 101 Report [39].

Prior Radiation Therapy to Tumor/Tumor Bed Site (Reirradiation): will use the following max dose point constraints (defined as dose to 0.035 cm^3^) [15]:

Larynx: ≤ 20 GySpinal cord: ≤ 8 GyMandible: ≤ 30 GyBrainstem: ≤ 8 GySkin: Dmax < 39.5 Gy

The treating physician has discretion when deciding between stated OAR constraints versus PTV coverage.

#### PULSAR treatment

Daily cone-beam CT will be obtained prior to radiation delivery to verify anatomic location and stability. Treatment will consist of 6, 10, or 15 MV photons directed at the PTV using HyperArc©’s automated non-coplanar VMAT technique. Patients will receive a total of 55 Gray in 5 fractions (biological effective dose with alpha/beta of 10: 115.5 Gray) to the PTV. Patients will receive each 11 Gray fraction of radiation every 14 +/−10 days. Treatment will be terminated early in cases of intolerable treatment-related toxicity, altered clinical context, or the patient declines further treatment.

#### Adaptive radiation planning

It is possible that patients will experience anatomical and/or tumor changes during the radiation therapy course such that patient alignment for radiation therapy is no longer optimized to the original CT simulation and radiation plan. In such cases where it is determined that adaptive planning is needed, we will abort planned radiation therapy and immediately perform re-simulation and offline re-planning if the anatomic change is significant enough to put adjacent normal tissue at significant risk; otherwise, we will re-plan offline with the next fraction of radiation to minimize treatment delays. Offline adaptive planning may include recontouring of target structures and/or OARs, and/or changes to the radiation prescription dose. This will be determined by the treating physician through standard of care clinical criteria and procedures. For patients who undergo re-simulation and re-planning, an extended window of 14 +21/−10 days from most recent radiation therapy fraction to receive the next radiation therapy fraction to accommodate re-simulation scheduling and re-planning time. The frequency of re-simulation and adaptive planning as well as associated changes in dosimetry will be measured and documented.

#### Cancer-directed systemic therapy

The following cancer-directed systemic therapy agents alone or in combination are permitted during and after PULSAR in the protocol:Chemotherapy: 5-FU, capecitabine, carboplatin, cisplatin, cyclophosphamide, docetaxel, doxorubicin, etoposide, gemcitabine, hydroxyurea, methotrexate, paclitaxel, vincristine.Targeted agents: Afatinib, cetuximab, dabrafenib erdafitinib, trametinib, vemurafenib.Immunotherapy: Atezolizumab, cemiplimab, durvalumab, ipilimumab, nivolumab, pembrolizumab, tislelizumab, toripalimab.

The specific timing of administration of these cancer-directed agents with respect to delivery of PULSAR fractions, including the decision to hold the agent throughout the entirety of the PULSAR treatment, will be determined at the treating physician(s)’ discretion. Other systemic cancer-directed agents not listed above are permitted at the treating physician(s)’ discretion.

Daily oral systemic cancer-directed agents (e.g. BRAF and MEK inhibitors) may be taken during PULSAR at a frequency determined by the treating physician(s). Example recommendations are provided in the following reference: Guimond et al. [40]*, **Adv Radiation Oncol*. However, coordination of stopping and starting daily oral medications around PULSAR fractions may be challenging, and holding such medications throughout the entirety of the PULSAR treatment is permitted at the treating physician(s)’ discretion.

